### Statistical methods

#### Sample size calculation

With a total sample size of 1370 patients (685 per arm), the study will have more than 90% power to detect a difference of 30 min in ED LOS, assuming an SD of 115 min. This calculation assumes a *t*-test with equal variance in both groups. This sample size will also give us 80% power to detect a 30 min between-group difference in subgroups of soft tissue injuries and fracture/dislocation, assuming 60% and 40% of patients with soft tissue injuries and fracture/dislocation, respectively. We believe the fracture/dislocation cohort may not accurately show the advantage of the primary-contact physiotherapy pathway as the LOS may be impacted by external factors such as waiting for an orthopaedic consult.

A difference of 30 min is considered clinically important based on previous evidence suggesting that 30 min was associated with a decrease in representation and ‘left without being seen’ rates.^25^ We also had input from local opinion leaders, including local ED directors who reported 30 min was clinically important and would impact patient flow. An SD of 115 min is consistent with a recent Australian study on quality indicators for musculoskeletal injuries in the ED.^26^ We do not anticipate any missing data for the primary outcome since LOS is routinely recorded for every patient presenting to an ED.

#### Effectiveness analysis plan

The main analysis of the primary and secondary outcomes will be conducted following the intention-to-treat principle, that is, by analysing patients according to their randomised group, regardless of post-randomisation events. The main analysis of ED LOS will be performed using linear regression adjusted for hospital using a random effect model. The effect of the intervention will be estimated as the adjusted mean difference and 95% CI. While ED LOS is unlikely to follow a normal distribution, the large sample size will allow us to make inferences about the mean difference. In case of important heteroscedasticity, as assessed using a plot of residuals against fitted values, we will conduct a sensitivity analysis using a log-transformation.

A detailed analysis plan including mock tables will be developed prior to unblinding. Analyses prespecified in the analysis plan will be programmed using randomly scrambled treatment allocations. Unblinded results will be presented to the study team once all analyses have been programmed and validated and the database locked. Analyses will be performed using SAS (V.9.4 or higher) or R (V.4.3.1 or higher).

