### Participants

All consecutive patients who present with a musculoskeletal condition to the participating EDs during the time the primary-contact physiotherapists are on shift will be screened by the physiotherapists for eligibility.

To be included in the trial, patients must fulfil all the following inclusion criteria: (1) adult patient 18 years or older; (2) present with a simple musculoskeletal condition. This would include, but is not limited to, soft tissue injuries (joint, ligament, tendon or muscle pain), musculoskeletal neck and low back pain, closed peripheral fractures not requiring reduction or orthopaedic fixation (indicated from triage notes), spontaneously reduced joint dislocations; and (3) have a triage score of either 3 (urgent), 4 (semi-urgent) or 5 (non-urgent) as per the Australasian Triage Scale (ATS). Patients with a triage score of 2 will also be included when presenting with an isolated joint dislocation, including shoulder, digit, patella or temporomandibular joint (indicated by triage notes).^17^

Patients will be excluded if presenting with at least one of the following exclusion criteria: (1) already assessed by a physician and/or a nurse practitioner in the ED as indicated on the electronic Medical Record (eMR); (2) any non-musculoskeletal/non-orthopaedic condition, such as open wounds, eye problems, foreign bodies and poisonings; (3) presentations outside the primary-contact physiotherapists’ working hours; (4) the triage notes indicate soft tissue injuries that may require surgical intervention; (5) the triage notes indicate a fracture requiring reduction and/or surgical fixation; (6) the triage notes indicate signs or symptoms of serious pathology (eg, spinal fracture, cauda equina syndrome, malignancy, infection or inflammatory origin of pain); (7) comorbidities requiring immediate emergency care (eg, cardiac, respiratory; or psychiatric issues as indicated on the triage note); (8) patient is unable to provide sufficient informed consent to participate (eg, cognitive impairment, intoxication, unable to understand spoken or written English) and (9) re-presentation of a patient who has already been included in the trial.

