### Patient selection and recruitment

Every person presenting to the ED with a musculoskeletal condition will be triaged by nursing staff and be recorded in the ED’s electronic patient list (Cerner FirstNet^®^). This triage process will not constitute a formal clinical assessment by a healthcare provider, such as a nurse practitioner. Throughout their shift, the physiotherapists will review the ED’s electronic patient list to identify potentially eligible patients. This is a normal practice for physiotherapists within EDs in Australia. For each patient where the visit reason in the triage notes suggests a musculoskeletal condition appropriate for primary-contact physiotherapy management, the physiotherapist will fill out an electronic eligibility form in the Research Electronic Data Capture (REDCap) database. If the patient is found to be eligible during the initial screening, the physiotherapist will inform the patient about the trial and provide the trial information flyer. A waiver of consent for screening and randomisation was granted by the Ethics Committee as this study is testing the effectiveness of two standard of care pathways on ED patient flow. Flow of participants is presented in figure 1.

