### Randomisation

All patients who fulfil the eligibility criteria will be randomised into the trial by the physiotherapist using REDCap. A 1:1 randomisation allocation sequence, incorporating randomly permuted block sizes of 2 and 4, and stratification by hospital site, will be generated prior to the commencement of the trial by an independent statistician not involved in participant recruitment, treatment, follow-up or statistical analysis using Statistical Analysis System (SAS) software. The randomisation schedule will be uploaded into REDCap to allow the randomisation to be performed online by the physiotherapist. Patients will be randomly allocated to either the primary-contact physiotherapy group (intervention group) or to the medical and/or nurse practitioner group (control group). REDCap will allocate each patient a participant ID number.

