### Data collection and study follow-ups

#### Data collection procedures

Health service outcomes and patient demographic characteristics will be extracted directly from the hospital eMR. Patient-reported outcomes will be collected via an online survey, supplemented by telephone calls. At days 1, 7 and 42 following randomisation, participants will receive a text message including a link for the e-Consent Form and online survey. One reminder message will be sent to non-responders at each follow-up time point. If no response is received, a trial research officer will contact them via telephone to complete the assessment.

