### Outcome measures

#### Primary outcome

The primary outcome for this trial will be ED LOS; defined as the period between when a patient presents at an ED, and when that patient is discharged from the ED.

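### The main ED LOS model adjusts for hospital only and gives up some precision that pre-randomisation covariates could recover; the estimate itself stays unbiased

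*Protocol article*

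**What the plan says.** The Effectiveness analysis plan section of the protocol article states: "The main analysis of ED LOS will be performed using linear regression adjusted for hospital using a random effect model". The abstract gives the same model. The effect is reported as an adjusted mean difference with a 95% CI, and a detailed analysis plan is promised before unblinding.

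The outcome clock is "the period between when a patient presents at an ED, and when that patient is discharged from the ED" (Primary outcome). Randomisation comes later than presentation. Patients are triaged and listed, and then: "Throughout their shift, the physiotherapists will review the ED’s electronic patient list to identify potentially eligible patients" (Patient selection and recruitment). Next, "the physiotherapist will fill out an electronic eligibility form in the Research Electronic Data Capture (REDCap) database". Only after that: "All patients who fulfil the eligibility criteria will be randomised into the trial by the physiotherapist using REDCap" (Randomisation). Allocation is stratified by hospital and by nothing else.

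Three patient characteristics are available before allocation:

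- **Triage category.** ATS category is an eligibility item (Participants).
- **Presenting condition.** It is screened from the triage notes (Participants; Patient selection and recruitment).
- **Age.** Adulthood is an eligibility item, and "Health service outcomes and patient demographic characteristics will be extracted directly from the hospital eMR" (Data collection procedures).

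**The concern.** The protocol itself gives reasons to expect these variables to relate to ED time. The Secondary outcomes section sets the benchmark waiting time by ATS category, and the Introduction says musculoskeletal patients wait longer because staff attend to more urgent cases first. The Sample size calculation section expects outside factors, such as waiting for orthopaedic advice, to affect LOS in the fracture/dislocation group. The Introduction also describes management and discharge planning as time consuming, above all in older patients with comorbidities. Neither the stratification nor the main model uses any of this.

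The pre-randomisation wait is a separate matter. It is an additive part of the outcome and is complete before allocation, so it is a legitimate baseline covariate. Left out, its contribution stays in the residual variance.

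At stake is the width of the primary confidence interval and, to a greater degree, power in the smaller subgroup for which the protocol makes a power claim.

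**Working it through.** **Inputs from the Sample size calculation section:** 685 per arm, SD 115 min, difference 30 min, subgroup shares 60% and 40%, no missing primary outcome. Two-sided alpha of 0.05 is assumed from the 95% CI, since alpha is not stated.

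**Step 1: the protocol's own figures.**

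- SE = 115 × √(2/685) = 6.21 min, so the 95% CI half-width is 1.96 × 6.21 = 12.2 min.
- Power = Φ(30/6.21 − 1.96) = 99.8%, consistent with the stated figure of more than 90%. A power of 90% would need 309 per arm (618 in total).
- 60% subgroup: 0.6 × 685 = 411 per arm, power 96.2%.
- 40% subgroup: 0.4 × 685 = 274 per arm, power 86.3%. The stated 80% is met in both. At alpha 0.025 the 40% subgroup would have 79.2%.

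**Step 2: what adjustment could add.** If the added covariates explain a share R² of the outcome variance, the residual SD is 115 × √(1 − R²). The documents give no R², so a range is assumed. The last column is 1370/(1 − R²), the unadjusted trial size with the same precision.

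| R² (assumed) | 95% CI half-width (min) | Primary power | 40% subgroup power | Equivalent unadjusted total |
|---|---|---|---|---|
| 0 (as planned) | 12.2 | 99.8% | 86% | 1370 |
| 0.02 | 12.1 | 99.8% | 87% | 1398 |
| 0.10 | 11.6 | 99.9% | 90% | 1522 |
| 0.20 | 10.9 | >99.9% | 93% | 1713 |
| 0.30 | 10.2 | >99.9% | 95% | 1957 |

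For R² = 0.02: 12.18 × √0.98 = 12.1. In the subgroup, SE = 115 × √0.98 × √(2/274) = 9.73 and Φ(30/9.73 − 1.96) = 87%. The subgroup column assumes that the same R² holds inside the subgroup and that its analysis uses the covariates. Condition group is constant there, so any gain must come from the others.

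**Step 3: the wait alone.** If the wait is uncorrelated with the later stay, R² = (wait SD/115)². Wait SDs of 15, 30, 45 and 60 min (all assumed) give 0.02, 0.07, 0.15 and 0.27. If each minute already waited shortens the later stay by half a minute, the slope of LOS on the wait is 0.5 and R² = (0.5 × SD/115)². That is 0.017 at SD 30 and 0.068 at SD 60. A positive correlation would raise R² instead.

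**Step 4: bias.** In 2000 simulated trials of 1370 patients at five hospitals, with a true effect of −30 min and a wait independent of the later stay, both models averaged −30 min to within about 0.1 min. Adding the wait cut the empirical SE from 6.11 to 5.91 min (about 3%) at a wait SD of 30 min, and from 6.21 to 5.30 min (about 15%) at 60 min.

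**The case against.** The strongest reply is that nothing here is wrong. The model adjusts for the only stratification factor, the mean difference is unbiased, chance imbalance is ordinary sampling error that the interval already covers, and the promised analysis plan may add covariates. Most of this stands. The point is about efficiency, not an error or a contradiction. But the article does fix the main model, in two places, so a later plan that added covariates would depart from it.

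Several stronger readings are tempting and are not supported:

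- **That the estimate is biased or the primary test underpowered.** Step 4 shows no bias, and primary power is about 99.8%.
- **That these are strong predictors.** The protocol makes a link plausible but gives no R², wait SD or age effect. Excluding patients already seen by a physician or nurse practitioner may also keep the wait short and its SD small.
- **That the wait is pure noise.** This needs zero correlation with the later stay. Control patients remain in the queue, so a longer wait already served may leave less to come. The documents do not settle the sign.
- **That the subgroups determined the sample size.** The text says only that the chosen size also gives 80% power in them, and it sets out no subgroup model.
- **That every variable is already recorded.** REDCap performs the randomisation and assigns an ID, but a stored randomisation time is not mentioned. The two condition groups are not said to be coded from triage notes rather than final diagnosis.

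**Conclusion.** The concern holds as a precision point. The main model omits ATS category, condition and age, which are known before allocation and which the protocol's own reasoning ties to ED time. It also omits a pre-randomisation wait that is part of LOS and beyond the reach of treatment. The size of the loss depends entirely on an R² that the documents do not give. It is negligible near 0.02 and worth having near 0.30, where the interval is about 2 min narrower on each side and the 40% subgroup gains about 9 percentage points of power. The validity of the primary comparison is not in question, and the stated subgroup power is already met at two-sided 0.05. The case for acting is that the gain is nearly free, leaves the estimand a mean difference in minutes, and can be prespecified cleanly only before unblinding.

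**What to change.** Before unblinding, prespecify the primary model as ED LOS on treatment and hospital (as planned), plus:

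- ATS category;
- age;
- condition group, soft tissue versus fracture/dislocation, classified from the pre-randomisation triage notes and not from the final diagnosis, with a rule for where neck and back pain belongs;
- minutes from presentation to randomisation, if REDCap holds a randomisation time. If it does not, leave this term out and keep the other three.

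Report the hospital-only model as a sensitivity analysis, so that the published primary specification can still be seen.

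No patients, visits or trial procedures are added. The work is some coding of triage notes, done blind to allocation, and linking REDCap times to eMR times. The sponsor should accept that the return may be modest.

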#### Economic evaluation

An economic evaluation, including cost-utility and cost-effectiveness analyses, of the primary-contact physiotherapy pathway compared with the physician and/or nurse practitioner pathway will be undertaken from the hospital perspective and according to the intention-to-treat principle. Data from the hospital on healthcare utilisation costs using presentation-level costing data will be collected. Intervention costs will be collected from trial records. Patient-level costing data will be calculated using the reported clinical and administrative activity received by each patient during their hospital visit. The method to collect intervention costs and the included costing data have been reported in our previous study.^27^ The effectiveness outcomes of the economic evaluation will be (1) quality-adjusted life-years (QALYs) gained over 6 weeks (cost-utility analysis) and (2) time spent in the ED avoided (cost-effectiveness analysis).

Utility-based quality of life will be measured using the EQ-5D-5L questionnaire,^22 23^ which has five domains with five levels each (mobility, self-care, usual activities, pain/discomfort and anxiety/depression), and the health utility score, which is expressed as an index value for health, will be calculated from the five domains for each participant in the trial using published Australian scoring algorithms.^28^ The score falls on the 0.0 (dead) to 1.0 (perfect health) value scale.

QALYs will be calculated using the health utility score calculated for the 6-week time point (day 42 post-trial randomisation).

The Incremental Cost-Effectiveness Ratios (ICERs) for each effectiveness outcome expressed as additional cost per (1) QALY gained at 6 weeks (cost-utility analysis) and (2) each additional person spending at least 30 min less in the ED (cost-effectiveness analysis) will be calculated using the mean costs and the mean health outcomes in each trial arm. Uncertainty around the ICERs will be explored using a non-parametric bootstrapping analysis (5000 replications) to generate 95% CIs that will be plotted on an incremental cost-effectiveness plane. Cost-effectiveness acceptability curves will also be estimated to show the probability that the primary-contact physiotherapy pathway is cost-effective compared with the usual care group and when considering different decision maker’s willingness to pay per QALY and for each additional person spending at least 30 min less in the ED. In Australia, there is no explicit willingness to pay threshold as it depends on the decision-making context; therefore, results will be presented using a cost-effectiveness acceptability curve, illustrating the probability of cost-effectiveness across a range of willingness to pay thresholds. Costs will be expressed in Australian dollars, adjusted for inflation using the Health Consumer Price Index as published by the Australian Bureau of Statistics. We will use multiple imputation methods to address missing data for the economic evaluation as suggested by Faria *et al.*^29^

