### Trial intervention and control

#### Primary-contact physiotherapy group (intervention group)

Following randomisation, patients who are allocated to the primary-contact physiotherapy group will be flagged in the eMR system. Recording who provides initial care in the system is a standard procedure in Australian EDs.

The physiotherapy intervention will be delivered by a senior physiotherapist (level 4 in Australia), a highly experienced clinician responsible for advanced patient assessment and management. As primary-contact clinician, they can independently diagnose and treat patients. In Australian EDs, a primary-contact physiotherapist is authorised to refer patients for diagnostic imaging and specialist consultations, with some jurisdictions also permitting them to prescribe a limited range of medications. Following an initial assessment, the primary-contact physiotherapist will choose the best course of management in consultation with the patient. In this trial, management of patients presenting with symptoms of low back pain will be provided following recommendations from the Australian Low Back Pain Clinical Care Standard.^19^ For any other musculoskeletal condition presentation, the clinical care will be guided by the best practice advice recommended by the NSW Emergency Care Institute.^20^

The primary-contact physiotherapist may consult an ED physician and/or nurse practitioner (collaborative model of care) or autonomously manage the clinical care of patients. In the autonomous model of care, the physiotherapist is the primary-contact clinician responsible for the patient assessment, management, diagnosis and discharge with no involvement of a physician and/or nurse practitioner. In the collaborative model of care, after selecting and assessing the patient, the primary-contact physiotherapist shares management and discharge decision-making with a physician and/or nurse practitioner.

In this trial, all patients will be provided with a discharge plan, including timely follow-up in the outpatient setting. Outpatient care will be provided by existing outpatient services such as outpatient physiotherapy, virtual hospitals, GP clinics, or specialist clinics, if required.

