#### Secondary outcomes

##### Health service outcomes

Time to clinical care; defined as time elapsed in minutes for each patient from ED presentation to the commencement of ED (non-admitted) clinical care.Duration of clinical care; defined as the period between when clinical care commences and the end of the (non-admitted) patient ED clinical care.Proportion of patients whose ED LOS is ≤4 hours (ie, proportion with care completed within 4 hours).Proportion of patients ‘seen on time’; defined as the proportion of presentations for which the waiting time to commencement of clinical care was within the benchmark time specified in the definition of the ATS category.^21^Proportion of patients admitted to the ED Short Stay Unit.Proportion of patients admitted to hospital inpatient units.Proportion of patients who received imaging.Proportion of patients who received opioids.Proportion of patients who received gabapentinoids.Proportion of patients who received specialist consult within the ED.Proportion of patients referred to specialist clinic.Proportion of patients re-presenting to the ED for the same chief complaint within 72 hours of discharge.Proportion of patients readmitted to the hospital inpatient units for the same chief complaint within 30 days of index inpatient admission.

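### The only cost window stated is the hospital visit, which is shorter than the 6-week QALY horizon in the same cost-utility ratio

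*Protocol article*

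**What the plan says.** The Economic evaluation section of the protocol article says that the evaluation "will be undertaken from the hospital perspective and according to the intention-to-treat principle". On the data source it says: "Data from the hospital on healthcare utilisation costs using presentation-level costing data will be collected". Its one rule for building a patient's cost is that it is calculated "using the reported clinical and administrative activity received by each patient during their hospital visit". The next sentence passes the detail to another source: "The method to collect intervention costs and the included costing data have been reported in our previous study".

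The effect measure for the cost-utility analysis is "quality-adjusted life-years (QALYs) gained over 6 weeks (cost-utility analysis", with utility taken at day 42 after randomisation. The incremental cost-effectiveness ratios (ICERs) "will be calculated using the mean costs and the mean health outcomes in each trial arm".

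Elsewhere the article records hospital use after the visit. Health service outcomes include re-presentation to the ED within 72 hours of discharge, referral to a specialist clinic, and "Proportion of patients readmitted to the hospital inpatient units for the same chief complaint within 30 days of index inpatient admission". The description of the intervention group says: "Outpatient care will be provided by existing outpatient services such as outpatient physiotherapy, virtual hospitals", and goes on to name GP and specialist clinics.

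**The concern.** A cost per QALY is interpretable only if costs and QALYs accrue over the same period and from the same perspective. Here the effect runs for 6 weeks. The single costing rule speaks of the visit, and no cost horizon in days or weeks appears anywhere. An ED re-presentation, a readmission or a hospital clinic attendance in week 2 is a hospital cost, so it falls within the declared perspective. It can also affect the utility measured at day 42. Under the stated rule its effect on health could enter the denominator while its cost stays out of the numerator.

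The two arms differ in who assesses, treats and discharges the patient. Later hospital use could therefore differ between them, and cost-effectiveness is both a stated objective and part of the hypothesis. The planned bootstrap and acceptability curves describe uncertainty in the costs that were collected. They cannot reveal costs that were not.

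**Working it through.** The article states no cost, QALY or ICER figure, so there is nothing of its own to reproduce. The check has two parts.

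**1. The statements side by side**

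- Perspective: hospital (Economic evaluation).
- Cost window: the hospital visit, in the singular; no end date (Economic evaluation).
- Effect window: 6 weeks, that is 42 days (Economic evaluation).
- Later hospital use that is recorded: 72-hour re-presentation, 30-day readmission, specialist-clinic referral (Health service outcomes). None is linked to the costing.
- Later hospital use that is expected: outpatient follow-up through existing services (Primary-contact physiotherapy group). GP care is one of these routes and lies outside a hospital perspective, so it is not part of this point.

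The recorded outcomes cannot stand in for costs to day 42. One stops at 72 hours. One counts readmissions only after an inpatient admission at the index visit. One records a referral, not an attendance.

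A Short Stay Unit or inpatient stay that arises from the index visit may already be costed. Only care after that episode is in question.

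**2. How sensitive the ratio is**

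The formulas are:

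- Time in years: T = 42 / 365.25 = 0.115.
- QALY difference = sustained utility difference × T.
- Omitted cost per patient = difference between arms in later events × unit cost.
- Shift in ICER = omitted cost / QALY difference.

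The utility differences, event differences and unit costs are all assumptions; none stands in the documents.

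- Utility difference 0.02: 0.02 × 0.115 = 0.0023 QALY.
- Utility difference 0.05: 0.05 × 0.115 = 0.0057 QALY.

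| Difference in later events | Unit cost | Omitted cost per patient | Shift per QALY, utility 0.02 | Shift per QALY, utility 0.05 |
|---|---|---|---|---|
| 0 points | any | A$0 | A$0 | A$0 |
| 0.5 points | A$500 | A$2.50 | A$1,087 | A$435 |
| 1 point | A$1,000 | A$10 | A$4,348 | A$1,739 |
| 2 points | A$1,000 | A$20 | A$8,696 | A$3,479 |
| 3 points | A$5,000 | A$150 | A$65,223 | A$26,089 |

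For example, 0.03 × 5,000 = 150, and 150 / 0.0022998 = 65,223. If the excess in later use is in the intervention arm, the true ratio is higher than the one reported by the amount shown; if it is in the control arm, it is lower by that amount. (This takes the utility difference to favour the intervention.) The shifts are large because the 6-week QALY denominator is about 0.002 to 0.006, not because the costs are large.

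**The case against.** The best defence is that the text does not restrict costing to the first visit. It never says that later care is excluded. Presentation-level data describes the unit of extraction and could cover every presentation to day 42. The sentence after the costing rule sends the reader to an earlier study for the included items, and a condensed article may leave such detail there or to a health-economics plan. This stands as far as it goes: a reader might infer that later costs are definitely dropped, and the document does not establish that. But a citation for cost items does not set this trial's cost horizon, and the one rule that is stated points to the visit.

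A reader might also infer that the omission flatters the physiotherapy pathway, because patients leave sooner and go on to outpatient care. The document does not support that direction. All patients in the trial are to receive a discharge plan with outpatient follow-up, and control clinicians may refer to outpatient physiotherapy. The sample size section cites evidence that links 30 minutes to fewer re-presentations, and the hypothesis expects comparable health service outcomes.

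Nor can one say what share of any saving from a shorter ED stay would be lost, because the document gives no unit costs.

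Finally, the mismatch concerns mainly the cost-utility ratio. The second ratio uses an outcome confined to the ED stay, so it has no horizon conflict, although its numerator would also omit later costs.

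**Conclusion.** The point holds as a mismatch in the stated plan, not as a demonstrated bias. Followed literally, the section gives a cost per QALY whose numerator covers the hospital visit and whose denominator covers 42 days, and nothing in it extends the costs.

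The direction of any bias is unknown, and the bias vanishes if later hospital use is equal between arms. Under the assumed values the shift runs from zero to about A$65,200 per QALY at a utility difference of 0.02, and to about A$26,100 at 0.05, in either direction.

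The primary outcome, ED length of stay, is unaffected. The matter should be settled before unblinding, because the cost-per-QALY result cannot be interpreted until the cost horizon is known. If later costs are already intended, one sentence resolves it.

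**What to change.** State one horizon for the cost-utility analysis: all hospital activity from randomisation to day 42, costed from the hospital costing system. List what this includes: the index visit, any Short Stay Unit or inpatient admission, ED re-presentations, readmissions and hospital outpatient clinics. Say that GP and other non-hospital care lies outside the perspective. Keep visit-only cost as a secondary analysis, paired with the ED-time outcome.

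The change needs a few lines in the analysis or health-economics plan and a wider date range in the costing extract. The article says that the detailed analysis plan will be developed before unblinding, so there is a natural place for it. It also describes a code sheet that links trial records to medical record numbers for validation and audit; whether the approvals cover a wider costing extract should be confirmed. The downsides are more extraction work and more variable costs, and so wider intervals around the ratio.
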